### Intervention

#### First period

Patients included in the study will be referred for a nursing appointment by their GP. In this appointment, the nurse will take several anthropometric measurements and measure blood pressure, after patients have rested for 5 min (initially, two readings, but if the difference is >5 mmHg another reading will be taken, and the final measurement will be the mean of the two or three readings obtained). The same day, urine and blood samples will be collected. Later, after explaining to patients what ABPM involves, they will be fitted with a portable blood pressure monitor. Patients will be asked to carry out their normal daily activities with few restrictions and provided with a notebook for them to write down the main events in their day, as well as the time they woke up, went to bed, et cetera.

Twenty-four hours after placing the ABPM device, patients will be seen again by a nurse in their health centre, for the monitoring system to be removed. At this point, the nurse will provide patients with their corresponding medication pack, which will be assigned with the randomisation code and recorded in the EDC system. This pack will consist of a box with two containers, one holding the medication to be taken in the morning and the other that for bedtime. Both containers will have enough pills to complete the entire 2 months of treatment. On completion of the first month, the patients will be seen again by a nurse, for the first follow-up visit. The participants will be reminded of the importance of taking the medication as instructed, that they must bring back the medication containers even if they are empty, and that they should record in their notebook any symptoms that they have at any point during the month that could be adverse effects and the day on which they had them. Finally, a new appointment will be made for the following month, by the nurse.

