### Sample size

A sample size of 258 patients, with 129 in each group, will provide a statistical power >80% for detecting as significant (*P*< 0.05) a difference of 2.5 mmHg between the mean arterial pressure with bedtime and daytime administration, using a two-tailed Student’s t-test (standard deviation obtained from previous studies, with similar populations to that of our project and estimated to be 8 mmHg) [4].

A reduction of 5 mmHg in arterial pressure is considered to be clinically significant at the individual level, since it is associated with a decrease of 12.5% in the risk of cardiovascular events and of 16.7% in the risk of acute cerebrovascular accidents [7]. We expect that with bedtime administration at least 50% of patients will achieve this level of reduction in BP, and that there will be no changes during day-time administration. Under this assumption, the mean difference between the two groups would be at least 2.5 mm/Hg.

These calculations are based on the formula for calculating sample sizes in cross-over clinical trials developed by Donner (1984) [18]. It has been assumed that around 5% of the BP measurements will not be valid, that around 15% will be lost to follow-up and that the intra-subject correlation will be 0.5.

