### Analysis

First, an assessment will be made of the potential carry over effect of the treatment from the first period to baseline levels before the second period. The analysis will be carried out on an intention-to-treat basis, comparing the mean blood pressure at the end of the period of bedtime intake with that observed after the daytime intake, adjusting for the baseline blood pressure at the start of each period in all patients which at least have received one dose of treatment. Moreover, we will perform a per protocol analysis with only the patients have not change in their treatment within the 5-month period of the trial and have not been withdrawn. The effect attributable to bedtime intake will be estimated in terms of the difference in mean blood pressure between the two periods and the 95% confidence interval will be calculated using mixed-effect models analysis of covariance for repeated measures of blood pressure taken in each subject at the end of each of the periods. These models will include the patient as a random effect (intercept), to take into account the correlation between the two measurements in the same individual in each period. As well as adjusting for the baseline levels, we will adjust for potential confounding or modifying variables: changes in medication, period or sequence, age, sex, unhealthy habits as to be smoker or no smoker, risk factors as to be dipper or non-dipper comorbidity as diagnosis of dyslipemia, diabetes, stroke, peripheric arteriophaty or myocardial infarction and month of the year when the study is started. We will assess, by means of tests of interaction, the absence of a modifying effect of bedtime intake as a function of the period when patients took the ASA at this time.

A stratified analysis will be undertaken considering two groups, dippers and non-dippers, assuming that the prevalence of non-dippers in this population is 40%.

In the mixed-effect analysis, all the data available from each of the subjects included in the study will be considered, regardless of whether there is missing data. Values of missing data will not be imputed, except in the case of the baseline values for the second period, in which case they will be assigned the same value as the baseline measurements at the start of the study. It has been shown that this is more robust than other approaches to dealing with missing data.

All this analysis will be carried out using the SAS statistical package.

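### The imputation rule does not cover an invalid first ABPM, so a treated patient without one loses at least the period-1 record from the primary model

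*Protocol article*

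**What the plan says.** The Analysis section of the protocol article fixes four things:

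- **Population and model.** The intention-to-treat comparison is made "adjusting for the baseline blood pressure at the start of each period in all patients which at least have received one dose of treatment". It uses a mixed model on the end-of-period pressures with a random patient intercept.
- **Further covariates.** These include "risk factors as to be dipper or non-dipper". The recording that defines this class is not named.
- **Data used.** In the mixed model, "all the data available from each of the subjects included in the study will be considered, regardless of whether there is missing data".
- **Imputation.** "Values of missing data will not be imputed, except in the case of the baseline values for the second period". A missing period-2 baseline is filled with the patient's own study-start value.

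Other sections bear on this:

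- *Evaluation of results* voids a recording with more than 30% of its data missing, a gap above 2 h, or a night's rest shorter than 6 h or longer than 12 h.
- *First period* has the device removed after 24 h and continues: "At this point, the nurse will provide patients with their corresponding medication pack, which will be assigned with the randomisation code". It mentions no validity check or repeat recording at that visit, and a valid first ABPM is not an inclusion criterion.
- *Second period* describes a third ABPM before the second course of medication, so period 2 has its own measured baseline.
- *Sample size* states: "It has been assumed that around 5% of the BP measurements will not be valid".

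**The concern.** The first ABPM supplies the period-1 baseline and the fallback value for a missing period-2 baseline. It may also supply the dipper class. The imputation rule is closed: it names one exception, and a missing first ABPM is not it. Likelihood-based mixed models keep subjects with missing outcomes, but software deletes any record with a missing covariate.

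Take a patient with an invalid first ABPM and valid recordings at the end of both periods. The period-1 outcome was measured but cannot enter the model. What remains is at most a single period-2 record, which carries no within-patient contrast. The analysis run as written then does not use all available data from all treated patients, although the section says it will. At stake are some precision and agreement with the declared analysis set.

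**Working it through.** **The plan's own figure.** Inputs from Sample size: SD 8 mmHg, correlation 0.5, difference 2.5 mmHg, two-sided 5%, power above 80%, 5% invalid, 15% lost.

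- SD of the within-patient difference = 8 × √(2 × (1 − 0.5)) = 8.
- n = (1.960 + 0.842)² × 8² / 2.5² = 80.4, or 83 with the paired t-test.
- With losses: 83 / (0.95 × 0.85) = 102.8, so 103.

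The planned 258 is well above this, so the stated power holds. Dividing also by the 40% non-dipper prevalence gives 83 / (0.40 × 0.8075) = 257. That is close to 258, but the article does not state this link; it is an inference.

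**Which records survive the written rule, given both outcomes measured**

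| First ABPM | Third ABPM | Dipper class taken from | Period-1 record | Period-2 record |
|---|---|---|---|---|
| valid | invalid | any | kept | kept (fallback works) |
| invalid | valid | another recording | lost | kept |
| invalid | valid | first ABPM only | lost | lost |
| invalid | invalid | any | lost | lost (no fallback value) |

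Below, the second row is the softer reading and the third row the strict reading.

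**Counts.** Assume the 5% applies to the first ABPM.

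- Affected patients: 0.05 × 258 = 12.9. The range is 5.2 at 2% and 25.8 at 10% (both rates assumed).
- First and third both invalid, if independent: 0.05² × 258 = 0.6 patients.
- Ignoring all other losses, there are 2 × 258 = 516 records. The softer reading leaves 516 − 13 = 503 records and all 258 patients. The strict reading leaves 516 − 26 = 490 records and 245 patients.

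**Complete pairs.** Patients with both outcomes: 258 × 0.85 × 0.95² = 197.9. Those who also have a valid first ABPM: 197.9 × 0.95 = 188.0. About 10 bedtime-versus-daytime pairs are lost under either reading.

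**Variance.** Losing 5% of patients outright predicts a ratio of 1 / 0.95 = 1.053. Simulation agrees. Inputs: 258 patients, between- and within-patient variance 32 each, effect −2.5 mmHg, 15% lost (half before the end of period 1, assumed), each of the four ABPMs invalid at random, and a random-intercept model with treatment, period, baseline and dipper class. Mean SE of the bedtime effect:

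| Invalid rate | Strict | Softer | Baselines filled by overall mean | Variance ratio, strict | Variance ratio, softer |
|---|---|---|---|---|---|
| 5% | 0.612 | 0.606 | 0.596 | (0.612/0.596)² = 1.05 | (0.606/0.596)² = 1.03 |
| 10% (assumed) | 0.647 | 0.635 | 0.612 | (0.647/0.612)² = 1.12 | (0.635/0.612)² = 1.08 |

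Repeat simulations at 5% gave 0.610 to 0.613 (strict), 0.605 to 0.606 (softer) and 0.595 to 0.596 (filled), so the strict ratio is 1.05 to 1.06. No bias was visible.

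**Power.** Φ(2.5/SE − 1.96) at 5% invalid is 98.3% (strict), 98.5% (softer) and 98.7% (filled). At 10% it is 97.2%, 97.6% and 98.3%.

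**The case against.** The case for leaving the text alone has four parts.

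1. **All-data sentence.** It can be read as the usual remark that patients with incomplete repeated outcomes are kept. It speaks of subjects included in the study; the one-dose wording stands in an earlier paragraph of the section. This softens the conflict but does not remove it. The one-dose statement is attached directly to the baseline adjustment, so the model, the population and the imputation rule cannot all be followed for these patients.
2. **Condensed article.** The full protocol may require a check or repeat of a failed first ABPM before medication is handed over, and the data-quality section does mention follow-up of missing data. That could make the case rarer. The imputation rule itself, however, is stated outright as closed, so an analysis plan that filled the first baseline would contradict it.
3. **The 5% figure.** It is a sample-size assumption about measurements and is not tied to the first ABPM or to whole 24-h recordings. This stands, and the counts above are conditional on it.
4. **Small consequence.** This stands too: power moves by less than half a percentage point at 5% invalid.

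A reader might also infer that a patient with an invalid first ABPM has no baseline at all and leaves the primary model. The documents do not support that as a general statement. Period 2 has its own ABPM, a mixed model drops records rather than patients, and no section says that dipper class comes from the first recording.

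**Conclusion.** The point holds as a minor gap in precision and in the declared analysis set. Under the written rule, a treated patient with an invalid first ABPM loses at least the period-1 record and so the within-patient contrast. The whole patient is lost only if dipper class is fixed from the first ABPM, which is a natural reading but not a stated one, or if the third ABPM is invalid as well.

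If 5% of first ABPMs are invalid, about 13 of 258 patients are affected. The variance of the treatment effect is then about 3% (softer reading) to 5–6% (strict reading) larger than necessary. These figures also rest on invalidity at random and on the assumed timing of dropout.

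It would be wrong to infer bias between the sequences. The first recording is finished before the pack is handed over, so its validity cannot depend on the assigned sequence. Nor is the primary conclusion at risk, since power stays near 98%.

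**What to change.** In the Analysis section:

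- Extend the exception. Replace a missing study-start baseline pressure by the overall mean of all randomised patients, computed blind to sequence. The existing fallback for period 2 then always has a value to carry forward.
- Treat a missing baseline dipper indicator the same way when it serves as a covariate, using the overall proportion.
- Name the ABPM that defines dipper class.
- Leave outcomes un-imputed. Leave patients without a dipper class out of the stratified dipper/non-dipper analysis only.

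This costs a few sentences and a line or two of code, with no new visits or data, and should be settled before the blind is broken. The downside is slightly less efficient baseline adjustment for the few patients with a filled value, a smaller loss than dropping their measured outcomes.

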### Legal and ethical considerations

This clinical trial will comply with the following regulations: the 2008 version of the Declaration of Helsinki, the Spanish Royal Decree 223/2004 of 6th February and the recommendations of the Council of Europe (Good Clinical Practices for Clinical Trials and Medicinal Products in the European Community, 17th January 1997). The protocol of the clinical trial has been agreed on by the primary care research committee, approved by the Clinical Research Ethics Committee of Euskadi, which is the reference committee, and authorised by the Spanish Agency for Medicaments and Health Products.

Only the researchers involved in the study will have access to patient codes. In relation to this, we will comply with the Spanish Act 14/2007 of Biomedical Research and Royal Decree 1720/2007 of 21 December that approves the regulations on the Development of the Organic Act 15/1999 of 13 December on Personal Data Protection.

### Limitations

One of the main potential limitations of this study is the difficulty of carrying out a triple-blind, placebo-controlled trial, with a drug that is already available in the market. This will be overcome by contracting the Laboratorium Sanitatis to prepare special formulations of the drug and the placebo.

The other possible limiting factor is the difficulty of effectively coordinating a multicentre trial in primary care. To address this issue, we will draw on the broad experience of the PCRUB in coordinating research projects across the network, namely within redIAPP and CAIBER.

## Discussion

The aim of this clinical trial is to assess the efficacy of a very easy-to-implement intervention for reducing blood pressure, namely just changing of the time of ASA administration in patients who are already taking this drug for secondary prevention. The findings could notably contribute to achieving good control of BP and, thereby, decrease cardiovascular risk among hypertensive patients; which remains an outstanding challenge. In the 2010 PRESCAP study, it was found that there was only good control of both systolic and diastolic BP in 46% of the study population even though, overall, >63% were on more than one type of antihypertensive drug [19,20]. There is a direct relationship between BP and the risk of suffering cardiovascular events, a 10% increase in BP increasing the risk of suffering cardiac events by 33% and of suffering from a CVA by 50% [8].

Several interesting studies have been published that show that night-time administration of low-dose ASA significantly reduces BP [1,3,4]. Notably, there is a more marked reduction in non-dippers, with night-time ASA even modifying the circadian pattern of BP by up to 58%, transforming them into dippers [2]. This last point is of great importance given that there is a direct relationship between the night-time dip in BP and the risk of suffering cardiovascular events, these being more common in non-dippers [11-14]. To date, all the studies have been conducted in healthy individuals or people with mild hypertension receiving no drug treatment [1-4]; although the results have been very promising, the effect of bedtime ASA on patients under antihypertensive treatment has not been demonstrated, hence the importance and relevance of undertaking this study.

Although there is no consensus over the use of ASA universally as primary prevention, [8,21,22] many hypertensive patients are under treatment with low-dose ASA as an antiplatelet agent, having previously had cardiovascular events [6-8]. Further, among patients with high CVR, there is a higher proportion of non-dippers than in the low-risk population [23]. The aforementioned studies suggest that BP could be reduced in patients already taking low-dose ASA as an antiplatelet therapy for secondary prevention, and that the reduction would be even greater with bedtime administration, that is, just by modifying the time of intake of ASA with no need to add extra drugs to their treatment, and that the magnitude of the reduction might transform non-dipper patients into dippers. Taking into account that it has been demonstrated that there is an association between a reduction in the night-time dip in BP and an increase in cardiovascular risk [11-14], we can expect that CVR will also decrease in these patients, with an improvement in the circadian pattern of BP.

In this study, we will use ABPM devices for a 24-h period, as the mean arterial pressure measured by this method is the measure that has been found to be most strongly correlated with the risk of morbidity and mortality and of suffering target organ damage due to hypertension [24-26]. In the design of the study, we have decided to take four sets of ABPM measurements. We understand that this could be considered inconvenient for patients, but we think this number of measurements is necessary to ensure the quality and reliability of the data. We hope that, given that the candidate patients have had a cardiovascular event, take several drugs (in most cases) and are concerned to optimise their control over risk factors, they will be willing to collaborate.

With respect to adverse effects, we do not expect to have more or different effects to those associated with the intake of low-dose ASA and this drug was already being taken by the participating patients prior to the trial. According to several studies [1-4], taking this drug in the evening does not increase the rate of adverse effects. Moreover, in a study that was carried out using 1,300 mg of ASA, it was found by endoscopy that there were 37% fewer cases of gastric bleeding when the ASA was taken at night than when it was taken in the morning [27].

We believe that our study will provide interesting data for the scientific community, as it is exploring new effects of a widely used substance. The greatest beneficiaries will, however, be patients who may potentially be able to achieve better control of the one of the most important cardiovascular risk factors and improve their prognosis, without having to take other drugs and with no further adverse effects. What is more, from the economic point of view, the treatment under trial does not represent an additional cost and could even lead to savings in healthcare; since when BP is reduced, there is a decrease in cardiovascular risk and, subsequently, in cardiovascular events and patients may require fewer antihypertensive drugs to achieve adequate control of their BP.

### Trial status

The status of the trial at submission is 104 patients recruited.
